**Table 2 Overview of effect of albendazole treatment on *Loa loa* microfilaremia**

| Albendazole regimen (number of subjects)                                                           | Pre-Tx LLM (mf/ml)
Time of measurement
Range (Geom. Mean)                            | Efficacy (% geometric mean preTx values)                                                                                                              | Adverse events                                                                 |
|----------------------------------------------------------------------------------------------------|--------------------------------------------------------------------------------------------|-------------------------------------------------------------------------------------------------------------------------------------------------------|--------------------------------------------------------------------------------|
| 200 mg BID, 21 days (11)                                                               | 11:30-14:30
385 - 20200 (2369)                                                          | - 70%-20% over 3 mos post Tx start
- 20% at 6 mos                                                                                                  | Myalgia, arthralgia, pruritus, increased appetite, dizziness, calabar swelling |
| Placebo BID, 21 days (12)                                                                          | 236 - 27500 (3119)                                                                         | - 37%-192% over 3 mos post Tx start
- 84% preTx at 6 mos                                                                                           | Myalgia, arthralgia, pruritus, increased appetite                              |
| 600 mg, single dose (23)                                                               | 11:00 - 13:00
7 - 1377 (180)                                                            | - 60%-125% over 3 mos post Tx start
- 60% at 6 mos
- 57% at 10 mos                                                                              | No adverse events reported                                                     |
| Mebendazole, 100 mg BID, 3 days (24)                                                               | 3 - 5535 (195)                                                                             | - 70%-132% over 3 mos post Tx start
- 93% at 6 mos
- 86% at 10 mos                                                                              |                                                                                |
| 400 mg, QD, 3 days (48) 
- 180 days FU (37)
- placebo (28)
- 180 days FU (27) | 10:00 - 15:00
100 - 33837 (2550.3)                                                      | ALB: 90%-70% over 3 mos post Tx
90% at 6 mos
Plac: 105%-95% over 3 mos post Tx
>120% at 6 month                                              | No difference between albendazole and placebo treatment                        |
| Placebo, QD, 3 days (51)
- 180 days FU (40)
- 400 mg, QD, 3 days (36)
- 180 days FU (28)  | 164.3 - 24050 (5507.9)                                                                     | Plac: 98%-110 over 3 month post Tx
120% at 6 mos
ALB: 95%-65% over 3 mos post Tx
90% at 6 mos                                                |                                                                                |
| 400 mg, BID, 3 days (47)                                                               | 11:00-15:00
260 - 54180 (3800)
Subgroup of 12 with LLM >8000
8460 - 54180 (18594) | All subjects
71%-82% over 3 mos post Tx
91%-81% 6-9 mos post Tx
> 8000 PreTx
94-53% pre Tx over 3 mos post Tx
104%-89% 6-9 mos post Tx | Itching, abdominal pain, diarrhea
Increased ALT/AST on day 5                |
| Multivitamin                                                                                       | 240-46780 (3467)
Subgroup of 14 with LLM>8000
8640-46780 (15558)                     | All subjects:
98-83% over 3 mos post Tx
91-107% 6-9 mos post Tx
>8000 preTx
92-74% over 3 mos post Tx
82-114% 6-9 mos post Tx          | Itching, diarrhea                                                              |

1 Klion et al. 1993, 2 Kamgno, Boussineq 2002, 3 Tabi et al. 2004 (% in efficacy cell approximated from Figure 2 in the publication). 4 Tsague-Dongmo et al. 2002

The time course in LLM seen in these studies, comparison of the effect of different doses evaluated as well as significant intra-individual variation in the effect of a single albendazole

dose, suggest that multiple exposure of the *Loa loa* macrofilaria with albendazole at two month intervals may have the desired effect on the reproductive capacity of the macrofilaria. The safety data available show that a single dose of 800 mg has an excellent safety profile, consistent with other data on the safety of single doses of albendazole (see above).

This study will evaluate the effect of an albendazole dose of 800 mg, administered every two months 2 or 6 times, respectively.

## 4 STUDY GOAL, OBJECTIVES AND EXPECTED OUTCOMES

The goal of this study is to evaluate whether one or both of the evaluated albendazole treatment regimens are sufficiently effective in reducing *L.loa* parasitemia and safe to potentially be qualified as candidate for mass treatment for the reduction of LLM.

The primary objective of this study is to evaluate the efficacy of two different albendazole treatment regimens in sustainably reducing *L. loa* microfilarial load in subjects with high pre-treatment microfilaremia.

The secondary objective is to assess the safety of these treatment regimens in the study subjects in terms of frequency of adverse events by type and severity.

In case this proof of principal study shows that one or both of the two albendazole treatment regimens, but not the placebo treatment reduce microfilaria counts sustainably (i.e. for a period of at least 4 months) by  $\geq 50\%$  of pretreatment values, and the safety profile is, as expected based on the prior experience with albendazole, consistent with the requirements for mass treatment, the results will be discussed with the stake holders to decide on further studies to be conducted.

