**Table 1 Overview of severe or serious neurological events reported in the literature**

| Adverse event(s)
(Comments)                                                                                                                                                                                                               | Pre-Tx LLM
(mf/ml) | Pre Tx LLM count based
on                   | Source                 |
|----------------------------------------------------------------------------------------------------------------------------------------------------------------------------------------------------------------------------------------------|-----------------------|------------------------------------------------|------------------------|
| Grade 2 coma
(1/26 subjects with >30000mf/ml)                                                                                                                                                                                             | 163000                | Pretreatment measurement                       | Ducorps
et al. 1995 |
| Serious neurological reaction (disorders of consciousness, coma, incontinency, sensory deficits, hypertonia)
(2/>3242 subjects with LLM including 18 with geometric mean LLM of 83448 mf/ml, 2/160 subjects with LLM >30000)  | 50502
152940       | Pretreatment measurement                       | Gardon et
al. 1997  |
| PLERM                                                                                                                                                                                                                            | 36000                 | Extrapolated from mean
post-treatment level | MEC 2002               |

 17877 subjects were treated. *Loa loa* blood microfilaraemia was evaluated in 5500 (31%) subjects, including 18/20 with serious neurological reaction, of whom 58% (3242) were *Loa loa* positive (Gardon et al. 1997) and 160 (2.9%) had LLM >30000 mf/ml pre-treatment (Boussinesq et al. 1998).

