## **8 ASSESSMENT OF SAFETY**

### **8.1 Safety Variables**

All safety variables will be derived from the adverse events reported by the subjects and/or observed during the clinical evaluations.

The frequency of treatment emergent adverse events will be compared by type of adverse event, severity and relationship to study drug between treatment groups.

Serious adverse events will be tabulated by relationship to study drug and treatment group. Narratives will be provided for each event.

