#### 8.3.2 Treatment emergent adverse events

Treatment emergent adverse events are adverse events that occur after administration of the study drug.

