### 9.2.2 Safety analysis

Calculation of the proportion of subjects with AEs and SAE by treatment group, type of AE, gender, severity and relationship to study drug (see section 8.1).

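### Section 4 makes mass-treatment safety a condition for going on, but safety data tabulated by assigned arm leave event rates up to about 14% open even with 0/20 events, and miss an easy pooled analysis of doses 1 and 2

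*Protocol*

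**What the plan says.** Section 4 sets the goal of finding out whether a regimen is effective and "safe to potentially be qualified as candidate for mass treatment for the reduction of LLM". Safety enters as a secondary aim, worded as follows: "assess the safety of these treatment regimens in the study subjects in terms of frequency of adverse events by type and severity". The condition for going on has two parts. One is a sustained fall in microfilaremia on albendazole but not on placebo. The other is that "the safety profile is, as expected based on the prior experience with albendazole, consistent with the requirements for mass treatment". If both are met, "the results will be discussed with the stake holders to decide on further studies to be conducted".

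On analysis, section 8.1 states: "The frequency of treatment emergent adverse events will be compared by type of adverse event, severity and relationship to study drug between treatment groups". Section 9.2.2 gives: "Calculation of the proportion of subjects with AEs and SAE by treatment group, type of AE, gender, severity and relationship to study drug". Section 8.3.2 defines the events counted: "Treatment emergent adverse events are adverse events that occur after administration of the study drug". Neither 8.1 nor 9.2.2 refers to the treatment given at a particular round.

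The table in section 6.2.1 shows Groups 2 and 3 both on albendazole 800 mg at months 0 and 2. From month 4 to month 10 Group 2 has four rounds of placebo and Group 3 four more of albendazole. Section 9.1 derives the sample size from the efficacy response only.

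**The concern.** Two features of the safety analysis limit what it can contribute to the section 4 condition.

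First, 20 subjects per arm is a small base for a statement about mass treatment. A clean table in one arm is compatible with event rates that nobody would call uncommon. The tables as described would not show this, because they carry proportions without limits.

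Second, tabulation by assigned arm over the whole study blurs the contrast of interest. Up to the month 4 dose, 40 subjects have an identical albendazole exposure, but they are reported as two sets of 20. Group 2's total then adds events from four placebo rounds, which pulls its proportion toward that of Group 1.

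Prior experience cannot fully make up for this in the population enrolled. By section 3, the 22810 subjects in the short-course safety base were in intestinal helminth trials, and the 21-day loiasis study had nobody above 30000 mf/ml. In Table 2, the 3-day study at 400 mg twice daily had 12 albendazole subjects above 8000 mf/ml. This trial enrols only above 15000 mf/ml and takes the highest counts first (section 6.1.3.4). At stake is how the safety result is read when further studies are discussed.

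**Working it through.** **The plan's own figure.** No safety figure is stated, so the only one to reproduce is the efficacy size in section 9.1: placebo rate 1/10^6, active rate 50%, two-sided alpha 0.025, power 90%, 16 per arm. The normal approximation gives n = [2.241·√(2·0.25·0.75) + 1.282·√(0.5·0.5)]² / 0.5² = 16.2, so 17. Exact power at 16 per arm is 96.2% (Pearson chi-square) or 89.5% (Fisher). Dropout: 16/0.8 = 20. The figure reproduces.

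**Zero-event bounds.** With 0 events in n subjects, the one-sided 95% upper limit is 1 − 0.05^(1/n) and the two-sided one is 1 − 0.025^(1/n).

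| n | one-sided | two-sided |
|---|---|---|
| 20 (one arm) | 13.9% | 16.8% |
| 40 (Groups 2+3) | 7.2% | 8.8% |

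**Precision of the by-arm difference.** With equal observed rates r in two arms of 20, the 95% half-width is 1.96·√(2r(1−r)/20): 19 points at r = 10%, 25 at 20% and 30 at 36% (the last is the placebo rate for three symptoms in the 21-day loiasis study, section 3).

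**Power of the by-arm comparison** at 20 vs 20. The two-sided 5% level and all rates are assumptions, because the protocol gives none; values are exact, Pearson / Fisher.

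- 10% vs 30%: 36% / 24%
- 20% vs 40%: 29% / 19%
- 0% vs 20%: 59% / 37%
- 0% vs 30%: 89% / 76%

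Excesses of 20 points would often be missed; very large ones would usually be seen.

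**Rare events, for scale only.** Table 1 quotes "2/160 subjects with LLM >30000" for ivermectin. At a rate of 2/160 = 1.25%, the chance of no event is 0.9875^20 = 78% in one arm and 0.9875^40 = 60% in two. This is not an estimate for albendazole.

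**What splitting and mixing cost.** Assume independent rounds with an event probability a per albendazole dose and b per placebo dose. Then:

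- Group 1, whole study: 1 − (1−b)^6
- Group 2, whole study: 1 − (1−a)²(1−b)^4
- Groups 2+3, doses 1-2: 1 − (1−a)²
- Group 1, doses 1-2: 1 − (1−b)²

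With a = 20% and b = 5%, the whole-study proportions are 26.5% (Group 1) and 47.9% (Group 2); over doses 1-2 they are 9.75% and 36.0%. Exact power (Pearson, two-sided 5%):

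| a / b | Group 2 vs 1, whole study | Groups 2+3 vs 1, doses 1-2 |
|---|---|---|
| 10% / 5% | 9% | 12% |
| 20% / 5% | 29% | 63% |
| 30% / 10% | 26% | 71% |

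In the 20%/5% case, restricting Group 2 to doses 1-2 already lifts power from 29% to 53%, and pooling takes it to 63%. At lower rates the gain disappears: with 5%/2% (11.4% vs 16.8% whole study; 4.0% vs 9.75% for doses 1-2) power is 7% against 4%. Group 3 is not diluted. In the 20%/5% case its whole-study proportion is 1 − 0.8^6 = 74%, far from placebo.

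**The case against.** A reader might infer that section 4 declares a regimen safe for mass treatment, that it does so on a between-group test, and that finding no difference counts as safety. The text supports none of these. Meeting the condition leads to a discussion about further studies of a potential candidate. Section 11.4 calls the trial a small proof of concept and wider use premature. Section 4 refers to prior albendazole experience and names no comparison; the comparison is in 8.1, without a test or acceptance rule. The profile can be judged from severity grading, causality assessment and the narratives for serious events. All of this stands.

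It is also fair that confidence limits and extra tables are commonly left to an analysis plan, that reporting by randomised arm is the normal default, and that the start time of each event is recorded (section 8.2), so a table by round stays possible. The ivermectin rates belong to a fast-acting microfilaricide and do not carry over to albendazole. The zero-event bounds describe this trial alone, not the total evidence.

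What remains is narrower. The protocol fixes the section 4 condition and describes safety tabulation by assigned arm. At this size that tabulation says little, and a better use of the same data is available in the population where prior data are thinnest.

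**Conclusion.** The concern holds in a limited form. The trial's own safety evidence cannot rule out event rates up to about 14% in one arm even with no event (16.8% two-sided), and the by-arm tabulation discards the identical early treatment of Groups 2 and 3. Pooling over doses 1 and 2 roughly halves the zero-event bound, to 7.2%. That result needs no assumption about rates, only that all 20 subjects per arm are dosed. The power gain (29% to 63%) does rest on assumed per-dose rates: it ranges from 9% against 12% to 26% against 71%, and vanishes when rates are very low. The dilution affects Group 2 only. No decision rule is wrong and no analysis is invalid; this is a low-cost improvement worth making.

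**What to change.** - **Section 9.2.2, by arm:** keep the tables. For any, severe, serious and neurological events, add exact 95% confidence limits per arm and a 95% confidence interval for the difference from placebo.
- **Section 9.2.2, pooled:** add Groups 2+3 (40 subjects) against Group 1 (20) for events from dose 1 until the month 4 dose, with the same limits.
- **Section 9.2.2, by round:** tabulate day 0-7 events by the treatment given at that round. This also places correctly any round at which a subject received albendazole for intestinal helminths (section 6.1.6.2).
- **Section 4:** state that the trial's safety conclusion is limited to what these upper limits exclude and is read together with the external albendazole data.

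The cost is wording in two sections and a few tables from data already collected, with no extra subjects or visits. There are two downsides. The safety statement will look weaker, and the pooled analysis covers doses 1 and 2 only. Cumulative exposure to six doses still rests on Group 3's 20 subjects.

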## 5 STUDY DESIGN

### 5.1 Overview

This is a randomized, double blind, placebo controlled field-based study of subjects infected heavily with *L. loa* who are otherwise of good health and live in an area not endemic for onchocerciasis or lymphatic filariasis. An area not co-endemic with onchocerciasis was selected because all areas endemic for onchocerciasis in Cameroon are either already conducting or are initiating CDTI and ivermectin treatment reduces *Loa loa* microfilaremia (see section 3) making it impossible to find subjects with high LLM. Furthermore, since ivermectin is an effective *Loa loa* microfilaricide, the effect of albendazole on LLM can only be evaluated if during the study period the subjects do not take ivermectin. Enrolling subjects co-infected with *Onchocerca volvulus* in this study would mean that for the around 20 months duration of the study, these subjects would be deprived of the benefit of ivermectin treatment, which should be administered at least on a yearly to maintain *Onchocerca volvulus* microfilaria levels below those where symptoms and potentially disease progression occur.

Selection of an area endemic for lymphatic filariasis and highly endemic for loiasis is not possible, because the data from the recently conducted survey for the distribution of lymphatic filariasis in Cameroon have been deemed to be unreliable.

While the medical need for a LLM reducing treatment is greatest among populations living in areas co-endemic for loiasis and onchocerciasis and/or lymphatic filariasis (see section 3), populations living in areas endemic only for loiasis will also benefit from a treatment that safely reduces LLM and thus presumably reduces the signs and symptoms and potentially long-term sequelae of loiasis. Among these populations particularly the subjects with high *Loa loa*

microfilaremia, such as those selected for this study, will benefit from the qualification of an LLM reducing treatment.

60 males and non-pregnant females between 18 and 65 years with an LLM of >15 000 mf/ml will be enrolled in this study and randomized by pretreatment LLM to one of three treatment regimens:

- Placebo Control (Group 1)  
these subjects will receive 6 oral doses of placebo, one every two months
- 2 doses of albendazole (Group 2)  
these subjects will receive 2 oral doses of albendazole (800 mg) 2 months apart, followed by four doses of placebo every two months
- 6 doses of albendazole (Group 3)  
these subjects will receive 6 oral doses of albendazole (800 mg), one every two months

Prior to each administration, subjects will undergo a pregnancy test, if applicable, as well as a clinical examination, quantitation of *L. loa* parasitemia and be asked about any adverse events since the last visit. If they show signs and symptoms of intestinal helminths, the stool will be examined. If clinically indicated or indicated based on the report of adverse event(s) by the subject, a full blood count and laboratory evaluations will be performed as appropriate. Follow up for adverse events will be conducted at the day of treatment, day 3 and day 7 after each treatment as well as at the next treatment and/or efficacy follow up visit.

Efficacy will be evaluated via microfilaria counts in a calibrated blood smear obtained prior to each administration as well as 4 months and 8 months after the last dose was administered. To account as much as possible in a field based study for the effect of the diurnal periodicity of the *L. loa* counts in the peripheral blood (), the calibrated blood smear samples will be obtained between 11:00 and 15:00 and at around the same time of day in each village.

**Figure 1** *Loa loa* microfilaremia counts and diurnal change in *Loa loa* infected subjects treated with ivermectin in Cameroon

[figure not shown]

Non-CNS SAE: serious adverse events not affecting the central nervous system.

Following unblinding of the data and completion of the analysis, the villages will be informed about the outcome of the trial and what consequences can be drawn for further studies to qualify albendazole for treatment of loiasis.

## 5.2 Primary endpoint

The primary endpoint will be the proportion of subjects in whom there is a sustainable ( $\geq 4$  months) reduction in microfilaremia by  $\geq 50\%$  of pretreatment values at any time point post the first drug administration by treatment group.

## 5.3 Secondary endpoints

- Proportion of subjects whose microfilaria counts have been sustainably reduced to  $< 8100$  mf/ml by treatment group
- % of reduction in microfilaremia (range, median, Williams geometric mean) at each time point by treatment group by microfilaria level pretreatment and gender
- Microfilaria loads at each time point in each treatment group, compared by non-parametric tests because of the non-normal distribution of the *Loa* microfilaremia.
- Evolution of microfilaria counts in time

- Type, frequency and severity of adverse events (all adverse events and separate only those with a reasonable probability of relationship with study drug, see section 8.5).

## 6 METHODOLOGY

### 6.1 Selection of study population and acquisition of baseline data

The trial will be carried out in the South and Central provinces of Cameroon. Subjects will be recruited from villages in the Nyong and Soo and Mvila division. These areas are endemic for loiasis but without onchocerciasis and without lymphatic filariasis.

The schematics below provides an overview of the selection of the study subjects.

[figure not shown]

\* A general medical consultation will be offered to those who have medical complaints (including villagers who want medical consultation but do not want to participate in the preliminary survey for LLM) and some drugs will be available to treat subjects with any ailment that is amenable to treatment. Villagers will be referred to a health center if the ailment is not amenable to treatment by the study team. These examinations will not yield any data for the study.

